## Abstract

**Background:**

Maternal and newborn mortality in Pakistan remains as a major public health challenge. Pakistan faces significant infrastructure challenges and inadequate access to quality health care, exacerbated by sociocultural factors. Facility-based audit systems coupled with community engagement are key elements in achieving improved health system performance. We describe an implementation approach adapted from the World Health Organization audit cycle in real-world settings, with a plan to scale-up through mixed methods evaluation plan.

**Objective:**

This study aims to implement a locally acceptable and relevant audit system and evaluate its feasibility within the rural health system of Pakistan for scale-up.

**Methods:**

The implementation of the audit system comprises six phases: (1) identify facility and community leadership through consultative meetings with government district health offices, (2) establish the audit committee under the supervision of district health officer, (3) initiate audit with ongoing community engagement, (4) train the audit committee members, (5) launch the World Health Organization audit cycle (monthly meetings), and (6) quarterly review and refresher training. Data from all deliveries, live births, maternal deaths, maternal near misses, stillbirths, and neonatal deaths will be identified and recorded from four sources: (1) secondary-level care rural health facilities, (2) lady health workers’ registers, (3) community representatives, and (4) project routine survey team. Concurrent quantitative and qualitative data will be drawn from case assessments, process analysis, and recommendations as components of iterative improvement cycles during the project. Outcomes will be the geographic distribution of mortality to measure the reach, proportion of facilities initiated to implement an audit system for measuring the adoption, proportion of audit committees with community representation, and proportion of audit committee members’ sharing feedback regularly to measure acceptability and feasibility. In addition, outcomes of effectiveness will be measured based on data recording and reporting trends, identified modifiable factors for mortality and morbidity as underpinned by the Three Delays framework. Qualitative data will be analyzed based on perceived facilitators, barriers, and lessons learned for policy implications. Results will be summarized in frequencies and percentages and triangulated by the project team. Data will be analyzed using Stata (version 16; StataCorp) and NVivo (Lumivero) software.

**Results:**

The study will be implemented for 20 months, followed by an additional 4-month period for follow-up. Initial results will be presented to the district health office and the District Health Program Management Team Meeting in the districts.

**Conclusions:**

This study will generate evidence about the feasibility and potential scale-up of a facility-based mortality audit system with integrated community engagement in rural Pakistan. Audit committees will complete the feedback loop linking health care providers, community representatives, and district health officials (policy makers). This implementation approach will serve decision makers in improving maternal and perinatal health outcomes.

**International Registered Report Identifier (IRRID):**

DERR1-10.2196/49578

## Introduction

### Background

Pakistan is a low-income country with significant infrastructure challenges, poor allocation of government funding for health, poor access to essential health care services, low-quality health care services [1], sociocultural constraints, and a feudal system that affects all aspects of province life [2]. One of the main impacts of these governance and funding challenges relates to the health of mothers and their newborn children—2 cohorts that are already categorized as populations at high risk. The manifestations of this burden include a persistently high neonatal mortality rate, accounting for 57% of child deaths across the nation [3], with 41 out of every 1000 born babies dying before the end of their first month [4] and a maternal mortality ratio of 186 per 100,000 live births [5]. Pakistan’s perinatal, neonatal, infant, under 5 years, and maternal mortality rates remain unacceptably high, with estimates of >399,429 children dying per year [6]. Although efforts to improve the quality and timeliness of care in district and regional facilities are being made, progress has been painfully slow [7].

Audits and review systems, especially those with community engagement, are 2 key elements that have been shown to improve the health system’s performance and maternal and perinatal health outcomes for at-risk populations [8]. Audits provide a documented history of the events leading up to the death and highlight process failures amenable to process redesign and teachable moments to prevent similar untoward events. Introducing audits and reviews can reduce inpatient maternal mortality (adjusted odds ratio 0.85, 95% CI 0.73-0.98; 191,167 deliveries; moderate certainty evidence) and likely inpatient neonatal mortality (adjusted odds ratio 0.74, 95% CI 0.61-0.90; moderate certainty evidence) [9]. Findings from a meta-analysis of 7 pre-post studies of facility-based perinatal mortality audits in low- and middle-income countries indicated a reduction in perinatal mortality of 30% (95% CI 21%-38%) after introduction of perinatal audits [10].

The District Health Information System (DHIS) seldom records and reports mortality (eg, maternal mortality and neonatal mortality) and severe morbidity indicators consistently and reliably (eg, birth asphyxia and preeclampsia), leading to challenges in data completeness in capturing vital statistics through routine health and administrative data. Audit systems at the facility levels can provide for sustained improvements in the quality of provision and delivery of services. Community linkages and engagement ensure proactive and detailed discussion of the causes and modifiable factors leading to the deaths, essential for improved working relationships between community members, health providers, and policy makers [11]. Audits of stillbirths and neonates also contribute to achieving Every Newborn Action Plan goal for reducing stillbirths and neonatal deaths to <12 newborn deaths per 1000 live births [12].

### The Three Delays Framework for Maternal and Perinatal Mortality

Pregnancy-related maternal, neonatal, and infant mortality is attributed to delays in using the Three Delays framework [13] with time-related consequences—the “first delay” around the decision to seek medical care, “second delay” attributed to the time to reach the health facility, and “third delay” caused by receiving inappropriate care after reaching the medical facility [14-16]. In Pakistan, the “first delay” has been further divided into two subgroups: (1) delay in recognition of the severity of illness and danger signs contributed to 18% of all delays and (2) delays in decision-making by virtue of limited action of women to make decisions regarding their transfer to facilities contributed 34% [7].

The impacts of delays in care can be seen in the recent Verbal Autopsy and Social Autopsy mortality survey in Table 1. More than half of the deaths (26%-55%) occurred at the community level (the first delay), 4% to 13% of deaths occurred in route to the facility (the second delay), and the remaining occurred within health care systems (the third delay).

**Table 1 table1:** Locations of neonatal, child, and maternal deaths according to the unpublished Verbal Autopsy and Social Autopsy results (2019).

Indicators	Hospital, %	Other health provider or facility, %	In route to health provider or facility, %	Home, %	Others, %
Location of neonatal deaths	55.3	2.3	4.1	38.2	0
Location of child deaths	35	0.9	7.1	54.7	2.2
Location of maternal deaths	56.8	11.4	12.5	26.4	3

### History of Perinatal Audit Systems in Pakistan

Previous efforts to introduce facility audit systems by the Pakistan Ministry of National Health Services, Regulations, and Coordination have used the phased implementation of the Maternal and Perinatal Death Surveillance and Response to enhance reporting, recording, tracking, and auditing of deaths [17]. The World Health Organization (WHO) is currently assisting Khyber Pakhtunkhwa and Baluchistan provinces, and United Nations International Children’s Emergency Fund (UNICEF) is helping the Sindh province in implementing audit mechanisms, but results have not been made public. The United Nations brief on COVID-19 [18] and the Pakistan Health Report 2020 [19] have stated that the Maternal and Perinatal Death Surveillance and Response has great potential for success.

We hypothesize that a WHO audit cycle that is locally acceptable in close consultation with local community representatives and health care providers is feasible for implementing a robust audit system in rural settings. Specifically, we asked the following questions:

Is the implementation of facility-based maternal and perinatal mortality audits in combination with targeted community engagement feasible in rural Pakistan?Will the maternal and perinatal audits improve the reporting of deaths and maternal near misses at the DHIS health facilities?Will the audit systems help better identify medical and nonmedical factors of deaths and near misses, and how doable recommendations are implemented through integration of feedback loops within the health facilities and communities?Will the community-facility audit interaction improve the early referral proportions?

### Primary Objectives

The primary objectives include the following:

Identify and establish audit committees at health facility levels with integrated community engagement, andDetermine the feasibility of implementing an acceptable audit system with community representation in existing secondary health facilities and serving catchment populations.

### Secondary Objectives

The secondary objectives include the following:

Identification of “first delay” (care-seeking decision), “second delay” (identification and reaching the health facility), and “third delay” (receiving adequate care and treatment at facilities) among mortality and morbidity cases, andPropose solutions and record actions taken to improve the access to quality of care through integrated feedback loops within health facilities and communities.

### Primary Outcomes

The primary outcomes include the following:

Proportion of facilities initiated to implement an audit system for measuring the adoption of audit system,Proportion of audit committees with community representation and proportion of committee audit members sharing feedback regularly to measure the feasibility of the audit system, andQualitative narrative approach for acceptability and exploring the facilitators of and challenges in implementing audit systems.

### Secondary Outcomes

The secondary outcomes include the following:

Geographic distribution of mortality to measure the percentage coverage or reach in the implementation district,Change in trends in data recording and reporting to measure effectiveness,Categorization of mortality and maternal near-miss cases among Three Delays framework,Number of awareness sessions covering the proportion of the catchment population,Number of referrals in and out of the health facility,Number of transport mechanisms linked to health facilities by audit committee members, andProportion of health facilities implementing actionable recommended actions at the facility level.

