### Study Setting

The study will be conducted in 1 district—Matiari (Sindh) with a population of 770,040 (Pakistan Bureau of Statistics–2017). The district selection was based on the operational ease with past positive experiences in efficient rollout of health services. Moreover, the district health office (DHO) of Matiari is actively involved in DHIS feedback meetings to improve the data quality.

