##### Step 3: Analyzing the Information

The aim is to identify problems in the system that may have contributed to maternal death, stillbirths, and neonatal deaths, especially those that could have been averted. Data analysis will include quantitative components, such as identification of trends in rates and causes of death and geographic location. Qualitative analysis will provide additional insight into the problems that caused the deaths of individual cases and more general information about groups of deaths caused by similar contributing factors. The use of both types of data together will provide a more robust analysis of the problems and aid the audit committee to identify priorities for action.

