### Data Management and Analysis

The data collection tool will be developed in English and then translated into the local language to be administered to the local community visiting the health facilities. Data will be collected manually and entered through a specifically designed application. The application will be installed on laptop or desktop at each health facility under the supervision of project leadership. The Aga Khan University Data Management Unit will develop an electronic database that includes the filters and data quality check indicators. Data will be entered at the end of every week and uploaded onto the Aga Khan University Data Management Unit server. All data files will be stored for 5 to 7 years and then deleted according to organizational procedures for the permanent destruction of electronic and paper data.

Descriptive statistics will be used to estimate maternal, neonatal, and other key quantitative variables. The Three Delays framework will be used to categorize the identified modifiable factors. Action reports will be submitted based on the recommendations proposed by the audit committee. The data will be analyzed using Stata (version 16; StataCorp) and NVivo (Lumivero) software and password-protected Excel (Microsoft Corp) files. A unique code identifier will be assigned for the cases to be selected for discussion in audit meetings. The village name and health facility name will be kept confidential in audit meetings and, instead, codes will be used. In addition, regular meetings, planned dissemination of study findings including manuscript publication, stakeholder knowledge sharing workshop including community participation, and conference presentations will be conducted.

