### Limitations

Our project is unique with its focus on community engagement and representation integrated into the facility-based audit system. As such, it has strong implications for scale-up and uptake across Pakistan’s regional districts. Nevertheless, the primary limitation of this study is the recording of neonatal and maternal deaths and their complete medical history from health facilities. To overcome this challenge, there will be planned quarterly refresher training for the facility staff regarding source register apprising and DHIS. Moreover, in monthly audit cycles, the cases will be presented by audit committee members including community representatives. This will help support local ownership for facilitating and using existing resources. DHOs will ensure the presence, retention, and participating attitude of audit committee members. The implementation design includes quantitative and qualitative approaches, which can provide strong evidence for the impact generated by the audit system implementation.

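### As described, the study can show whether DHIS reporting changed but cannot attribute a change to the audit package, because no pre-audit window or comparator is stated

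*Protocol article*

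**What the plan says.** The second research question, at the end of the section on the history of audits in Pakistan, is: "Will the maternal and perinatal audits improve the reporting of deaths and maternal near misses at the DHIS health facilities". The matching entry under Secondary Outcomes is "Change in trends in data recording and reporting to measure effectiveness".

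On analysis, the abstract's Methods state: "Results will be summarized in frequencies and percentages and triangulated by the project team". Data Management and Analysis states: "Descriptive statistics will be used to estimate maternal, neonatal, and other key quantitative variables". Trends are also mentioned in Step 3 of the audit cycle: "Data analysis will include quantitative components, such as identification of trends in rates and causes of death and geographic location". Those are trends in mortality, not in reporting. The impact evaluation in Step 6 likewise concerns mortality and morbidity.

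On design, Study Setting states "The study will be conducted in 1 district" and adds that the district health office "is actively involved in DHIS feedback meetings to improve the data quality". Study Timeline gives 20 months of implementation and 4 further months so that neonatal and maternal outcomes can mature. No pre-audit period and no comparison facilities or district are described. Limitations announces that "there will be planned quarterly refresher training for the facility staff regarding source register apprising and DHIS", and closes by expecting the mixed design to deliver strong evidence of the audit system's impact.

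**The concern.** The research question is causal and the outcome is called a measure of effectiveness, but the stated summary describes only what was observed. If DHIS reporting rises over the 20 months, three explanations compete: the audit package, a drift that would have continued anyway, and season. The article itself names an activity that could produce drift, since the district office was already taking part in meetings aimed at better DHIS data. It also uses that involvement as a reason for choosing the district.

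What is at stake is the effectiveness claim that would support scale-up. A rise in percentages could be credited to the audits when it would have happened without them. The error can also run the other way. If audits reduce deaths, the number reported may stay flat while reporting improves.

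**Working it through.** The article gives no alpha, power, effect size or baseline reporting level, so there is no planned figure to reproduce. Three checks follow.

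**1. Can a change at launch be estimated?** For month t, a segmented model has four columns: intercept, t, an indicator for months after launch, and that indicator times months since launch. The post-launch period is 20 months (Study Timeline).

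| Pre-launch months | Rank of design (4 needed) |
|---|---|
| 0 (none is stated) | 2 |
| 1 | 3 |
| 2 | 4 |
| 6, 12 or 24 | 4 |

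With no pre-launch months the indicator equals the intercept and its product with time equals t, so level and slope change are not identified. No later choice of model repairs this without earlier data. Two months suffice algebraically, but a usable slope and a seasonal term need more, hence 12 to 24 below. Even at rank 4, a change that coincides with launch cannot be separated from other DHIS activity starting then unless there is a comparator.

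**2. What could drift alone produce?** This is an illustration on assumptions. From the article come the population of 770,040 and the national figure of 41 neonatal deaths per 1000. Assumed are a birth rate of 30 per 1000, DHIS completeness averaging 40% in the first 10 months, linear drift, no audit effect and two-sided alpha 0.05.

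- Neonatal deaths per 10 months: 770,040 × 0.030 × 0.041 × 10/12 ≈ 789. If only a quarter are in scope, n ≈ 197. Over 20 months, birth rates of 20 to 35 per 1000 give about 1,052 to 1,842.
- Apparent rise d, last 10 against first 10 months: d = 10 × monthly drift.
- Chance that a naive two-proportion test shows a significant rise: Φ((d − 1.96·SE0)/SE1), with SE0 = √(2p̄(1−p̄)/n) and SE1 = √((p1(1−p1)+p2(1−p2))/n).
- Example, drift 0.5 points a month and n = 789: p1 = 0.40, p2 = 0.45, SE0 = 0.02489, SE1 = 0.02486. This gives Φ((0.05 − 0.04878)/0.02486) = Φ(0.049) = 0.52.

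| Assumed drift, points per month | Apparent rise, points | n = 789 per half | n = 197 per half |
|---|---|---|---|
| 0 | 0 | 2.5% | 2.5% |
| 0.25 | 2.5 | 17% | 7% |
| 0.5 | 5 | 52% | 17% |
| 1.0 | 10 | 98% | 51% |

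A descriptive comparison would show the same apparent rise. Season does not cancel either: 20 months is one year plus 8 months, so the two halves cover different calendar months.

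**3. Is reported deaths per delivery a measure of reporting?** Reported deaths = true deaths × completeness. The Background section cites a 30% fall in perinatal mortality after audits (95% CI 21% to 38%). If true deaths fell by 30%, completeness would have to rise by a factor of 1/0.70 = 1.43 to keep the reported number level (1/0.79 = 1.27 to 1/0.62 = 1.61 over the interval). The ratio mixes two changes and cannot serve alone as the reporting indicator.

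**The case against.** The strongest reply is that this is a condensed article. A trend model, with its handling of autocorrelation and uncertainty, may sit in a full protocol or SAP that is not shown, and its absence here is not an error. That stands, so the point does not rest on a missing model. It rests on the stated design: one district, a timeline with no pre-audit window, no comparator, and a conclusion about impact.

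A second reply is that DHIS is an existing routine system, so earlier returns may be available, and an outcome worded as a change in trends is compatible with using them. This too is fair. The article does not confine reporting data to the intervention period; it does not state a reference period.

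Three stronger readings are tempting and are not supported:

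- A reader might infer that DHIS reporting in the district was already rising. Study Setting gives the purpose of the meetings, not a measured improvement.
- A reader might treat the refresher training as a confounder. The abstract makes quarterly review and refresher training the sixth phase of the intervention, so it belongs to the package. It matters only if the effect is credited to audit meetings alone.
- A reader might conclude that the second question cannot be answered at all. Whether reporting changed can still be described if earlier DHIS data or the four-source count is used; attribution is what is lost.

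**Conclusion.** The point holds for attribution. As described, a change in DHIS reporting could be shown but not assigned to the audit package, and the expectation of strong evidence for impact goes further than the design supports.

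The size of any bias is unknown. The drift table rests on assumed birth rate, completeness and drift. It runs from no distortion at zero drift to an apparent 10-point rise at 1 point a month, and nothing in the article says where in that range the district lies. The identification result (rank 2 of 4 without earlier months) needs no such assumption, only that no pre-launch series is used.

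The matter concerns one secondary outcome. The primary outcomes on adoption, feasibility and acceptability are unaffected. The change is worth making because a better analysis may be available from routine data.

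**What to change.** - State a pre-launch window, for example 12 to 24 months, and extract the monthly DHIS returns of the same facilities for it.
- Define reporting indicators that can be computed in both periods: monthly report submission, completeness of the death and near-miss fields, and reported counts of deaths and of near misses.
- Analyse them with a segmented time-series model with level and slope change at launch, allowing for season, facility and autocorrelation. Add non-implementing facilities as a comparison series where their returns are available.
- During the study, also report completeness as DHIS-reported events over the count from the four sources listed under Sample Size. Two of those sources, the audit committees' community representatives and the project survey team, belong to the project, so this ratio supplements the before-and-after series and does not replace it.
- Do not read reported deaths per delivery as reporting alone.
- Name the effect as that of the whole six-phase package, including refresher training.
- If no usable pre-launch series exists, limit the second research question and the closing claim under Limitations to descriptive statements.

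The cost is retrieval of routine returns and one additional model. The downside is that early DHIS data may be sparse or unreliable: the Introduction itself says that DHIS seldom records these indicators consistently. The quality of the earlier months should therefore be checked before the model is relied on.

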### Sample Size

Population size is a challenge in the rural setting, however this study intend to cover all records of stillbirths, neonatal deaths, maternal deaths, and maternal “near misses” from four sources: (1) secondary health facilities, (2) LHW registers, (3) audit committee’s community representatives, and (4) project routine survey team.

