##### Step 2: Collecting Information

The aim is to empower designated staff to collect a standardized set of information from the patient file or register as soon as possible after the death. For every death, decisions will be taken regarding what information is recorded, where the information is recorded, who records it, and who collates it on a periodic basis both for the death review process and for reporting to other levels within the health system. It should be noted that if the use for the data cannot be identified, the data will not be collected. Before collecting the information, the audit committee will have a clear understanding of the data analysis plan to help identify the data to collect. Data abstraction or collection forms will be either electronic or paper-based, depending on the infrastructure and capacity of the health facility. Clear directions about the exact data and qualitative information that should be collected will be included.

All data collected will be stored on password-protected laptops or tablets or locked cabinets in locked offices within the health facility. Before implementation, data collection forms will be piloted and revised as needed. The minimum data collected will include the following: information about the mother’s condition, baby’s condition on admission and at the onset of labor (for antepartum and intrapartum deaths), baby’s condition at birth (stillbirth or live birth), baby’s condition on discharge from the health facility (alive, transferred to another facility, or dead], and date and time of birth and death (so that the age at death can be calculated in hours rather than days).

As part of the intervention, each facility audit system is planned to be comprehensive to ensure that it captures data on each death and includes the relevant cause of death; link to maternal condition; demographic data; and a list of contributing, modifiable factors corresponding to codes for analysis and linked to recommendations. To ensure that phase-1 and phase-2 delays are captured, all efforts to link deaths that occur in the community to the facility audit system will be conducted by the trained LHWs, CMWs, and project team. The audit committee will hold follow-up monthly meetings with designated community engagement members to initiate the chain of notifications within the audit cycle as it relates to the implementation of recommendations and solutions.

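### The fourth research question asks about early referral proportions, but the only referral outcome is a number of referrals with no timing criterion and no denominator

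*Protocol article*

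**What the plan says.** The article lists four research questions at the end of the section on the history of perinatal audit systems in Pakistan. The fourth is "Will the community-facility audit interaction improve the early referral proportions".

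Referral appears as an outcome once, under Secondary Outcomes: "Number of referrals in and out of the health facility". It is not in the primary or secondary objectives, the primary outcomes, the abstract's outcomes or the operational definitions. Nowhere does the article say what makes a referral early.

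Four other statements bear on the point:

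- **Delays.** A separate secondary outcome is "Categorization of mortality and maternal near-miss cases among Three Delays framework".
- **Possible denominator.** The abstract's Methods say "Data from all deliveries, live births, maternal deaths, maternal near misses, stillbirths, and neonatal deaths will be identified and recorded from four sources". Step 1 of the audit cycle also has deliveries and births entered in a source register.
- **Minimum data.** Step 2 of the audit cycle lists the baby's status on discharge ("alive, transferred to another facility, or dead"). The only times it names are those of birth and death. No time of referral or arrival is listed.
- **Analysis.** Data Management and Analysis says "Descriptive statistics will be used to estimate maternal, neonatal, and other key quantitative variables" and does not mention referrals.

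**The concern.** The question is about a change in a proportion that is defined by timing. The outcome is a number without timing. These are different quantities, and one does not determine the other.

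The number is also hard to interpret by itself. Referrals in may rise because families seek care sooner, or only because more women use the facility. Referrals out may rise because staff recognise problems better or because the facility has lost capacity, and may fall because it can now manage more cases itself. A reader shown a rise or a fall could not tell improvement from deterioration.

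At stake is one of the four stated research questions. If data collection follows the outcome list, the study may end with a referral count and no means of saying whether referral became earlier. A timing item that was never recorded cannot be recovered at analysis.

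**Working it through.** The article states no referral figure, so there is nothing to reproduce. The check compares the wording and then illustrates the consequence with assumed numbers.

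**1. Question against outcome**

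| Element | Research question 4 | Listed outcome |
|---|---|---|
| Type of measure | Proportion | Number |
| Timing criterion | Early (not defined) | None |
| Denominator | Implied, not named | None |
| Direction of referral | Not named | In and out |

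Elsewhere in the primary and secondary outcome lists the authors write 'proportion' where they mean one, so 'number' cannot safely be read as shorthand for a proportion.

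**2. Could another item in the article supply the missing quantity?**

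- *Three Delays categorization.* It deals with timing, but only among deaths and near misses. A woman who is referred early and so avoids both is the success the question is looking for, and she is not in that set.
- *Recorded deliveries.* They permit referrals per delivery, which adjusts for attendance but says nothing about early referral.
- *Minimum data set.* The times listed are those of birth and death. The one transfer item is the baby's status on discharge. Neither dates a referral in.

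**3. Illustration (all inputs assumed)**

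Period 1: 1,000 deliveries and 100 referrals, 40 of them early. Period 2: 1,500 deliveries and 150 referrals, with either 60 early (scenario A) or 40 early (scenario B).

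| | Period 1 | Period 2, A | Period 2, B |
|---|---|---|---|
| Number of referrals | 100 | 150 | 150 |
| Change in number | – | 150/100 − 1 = +50% | +50% |
| Referrals per delivery | 100/1,000 = 10% | 150/1,500 = 10% | 10% |
| Early share of referrals | 40/100 = 40% | 60/150 = 40% | 40/150 = 26.7% |

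The number rises by 50% in both scenarios and referrals per delivery stay at 10% in both, while the early share is unchanged in A and falls by 40 − 26.7 = 13.3 percentage points in B. Neither the count nor the count per delivery tells the two apart.

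**4. A timing field without a denominator is not enough either**

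Suppose all referrals rise by 20% and the early share falls from 40% to 35%. The number of early referrals changes by a factor of 1.20 × 0.35 / 0.40 = 1.05. It rises by 5% although the proportion has worsened. A count of early referrals is not the article's outcome; the example shows only that the timing field and the denominator are both needed.

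**The case against.** The strongest reply is that a condensed article leaves register fields and definitions to the full protocol, the forms or the analysis plan. Step 2 describes only a minimum data set and says forms will be piloted and revised, so the absence of a referral time there does not prove that none is planned. The abstract promises frequencies and percentages, and deliveries are recorded, so some referral percentage can be derived. Timeliness is partly covered by the delay categories, and deaths and near misses are the study's eligible cases.

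Much of this is fair. The missing time stamp alone would not be a finding. What remains is that two statements in the article disagree: it asks about one quantity and lists another as its outcome. A percentage per delivery does not measure early referral, and the delay categories leave out women whose early referral worked.

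Two stronger readings are tempting and are not supported:

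- *That referrals in and out will be added together, so that opposite signals cancel.* The outcome names both directions in one item but does not say they will be summed; two separate counts are the more natural reading.
- *That the denominator must be all women and newborns with a complication.* The question names no denominator. Early referrals among all referrals in fits its wording equally well, and the article does not provide for a register of every complication.

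**Conclusion.** The mismatch is real. As written, the referral outcome cannot answer the fourth research question, because it lacks a timing criterion and a denominator, and a change in it is compatible with an unchanged or a worse early share.

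The size cannot be given from the document, which reports no referral data. The 40% against 26.7% contrast rests on assumed inputs, but the conclusion follows from the form of the outcome and does not depend on them.

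The reach is limited. This is one secondary outcome in a descriptive feasibility study, and referral is in none of the stated objectives. The primary outcomes on adoption, community representation, feedback and acceptability are unaffected. The outcome should be changed, but the design is not undermined.

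**What to change.** 1. Restate the outcome as a monthly proportion per facility, with referrals in and referrals out reported separately.
2. For referrals in, report early referrals divided by all referrals in. Define early in advance, and capture it with one arrival-status or timing field in the source register.
3. Also report referrals in per recorded delivery and referrals out per recorded delivery. Deliveries are already collected.
4. Keep the counts as supporting data.
5. If referral timing cannot be recorded, reword the fourth question to match the count and draw no conclusion about early referral.

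The cost is a definition in the outcome list, one added field and slightly more register work. A denominator of all registered complications is not required, nor is tracing every woman or newborn referred out to 28 or 42 days; either would cost considerably more than one field.
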